#### Primary objective

The diagnostic accuracy of the DelApp versus the reference standard will be determined using sensitivity, specificity, and positive and negative predictive values. The DelApp total score will be analysed in a univariate logistic regression and ROC curve analysis. From this we will obtain a measure of the discriminating ability of the DelApp score, by calculating the Area Under the ROC Curve (AUC). We will also calculate the optimal cut-off using Youden’s index [23] to assess if the a priori DelApp cut-off scores are appropriate. These a priori DelApp cut points are 8 for discriminating delirium from the whole sample, and 6 for discriminating between delirium and dementia [2].

#### Secondary objectives

Using Spearman correlations, we will evaluate the association between DelApp scores with delirium severity as measured with the DRS-R98 (secondary objective A) and tests of attention (digit span, months of the year backward, days of the week backward, and Vigilance A’; secondary objective B) to investigate construct validity.

To assess criterion validity, the association between DelApp total scores and length of stay, mortality at 12 weeks after study participation and discharge location will be evaluated with normal linear models (secondary objective C).

To explore the performance of the DelApp in tracking change in attentional functioning and delirium status, changes in test scores over time (from patients who have undergone repeat assessments), rescaled to a common range of values to facilitate comparison between tests, will be presented in descriptive statistics and graphically, comparing baseline with each of the other time points (secondary objective D).

Inter-rater reliability will be evaluated using the Kappa statistic and its 95% CI (secondary objective E).

Participants with missing data on the primary outcome measures will be removed from the statistical analysis. In case of a high proportion of missing data we will consider an imputation approach.

All statistical tests will be two-sided and will be performed using a 0.05 significance level and 95% (two-sided) CIs will be presented. There will be no statistical adjustment for multiplicity of analyses; there is a single primary analysis and the interpretation of secondary analyses will be suitably cautious to reflect the large number of variables considered.

For all statistical analyses, the primary analyses will be unadjusted. We will also present secondary analyses adjusted for age, sex, centre and IQCODE.

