### Study aims and objectives

The *primary objective* is to evaluate the diagnostic accuracy of the DelApp in a representative sample of patients versus the reference standard. A priori cut points for discriminating delirium from the whole sample and from dementia, derived from preceding case-control studies [23], will be evaluated.

The *secondary objectives* are:A.To evaluate the DelApp total score as a measure of delirium severity (construct validity);B.To determine the association between DelApp total scores and other measures of attention (i.e. months of the year backward, days of the week backward, Vigilance A’ test and counting down from 20 to 1) (construct validity);C.To assess if DelApp scores predict important clinical outcomes: length of stay, mortality at 12 weeks and discharge destination;D.To determine if DelApp scores are responsive to changes in delirium status and severity for a person over time.E.To assess inter-rater agreement of the DelApp assessment.

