## Methods

### Study overview

This is a diagnostic accuracy study involving a representative sample of patients recruited from general and acute medical hospital wards. We aim to recruit 500 patients aged 65 years and over from the Royal Infirmary of Edinburgh and the Glasgow Royal Infirmary, Scotland, UK. We expect that at least 100 patients will have delirium [3], and a similar or greater number will have dementia without delirium [24]. All patients will be screened in order of arrangement of beds on the respective wards with no limit on duration of patient stay, subject to researcher availability. Informed consent will be sought from patients or their relatives or welfare guardian. The study overview flowchart is shown in Fig. 1.

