### Sample size calculation

Of the 500 patients recruited, 20% would be expected to have delirium [3]. Sample sizes were obtained using a normal approximation to the binomial distribution to estimate a 95% confidence interval (CI) for measures of diagnostic accuracy for delirium. The anticipated confidence interval widths are shown in Table 2 for a range of levels of diagnostic test performance.

**Table 2 Tab2:** Precision of sensitivity and specificity estimation (delirium versus control comparison)

Sample size	Parameter	True level of parameter	95% CI width
500	Sensitivity	0.5	±0.098
	Sensitivity	0.7	±0090
	Sensitivity	0.9	±0.059
	Specificity	0.5	±0.049
	Specificity	0.7	±0.045
	Specificity	0.9	±0.029

The sensitivity precision in the delirium versus dementia comparison will be identical to the details outlined above, as the size of the delirium target group is unchanged. The dementia group is similar in size to the delirium group, hence the precision of specificity estimation in this comparison will be similar to that given for *sensitivity*. These estimates are based on a delirium prevalence of 20%

In a sample of 500 patients, as per the original study protocol, specificity for the delirium versus no delirium comparison and the delirium versus dementia comparison can be estimated precisely in all scenarios; sensitivity can be measured precisely when the diagnostic performance is good, and moderately precisely in other scenarios (Table 2).

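### Objectives A and D: a Spearman correlation not split by delirium status can arise from group separation alone, and the change summaries are not linked to each patient's own change in delirium

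*Protocol article*

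**What the plan says.** **Objective A.** Study aims and objectives sets the aim of evaluating the DelApp total score as a measure of delirium severity, under construct validity. The analysis, in Secondary objectives of the Statistical analysis plan section, is: "Using Spearman correlations, we will evaluate the association between DelApp scores with delirium severity as measured with the DRS-R98". No subset or stratum is named. The adjusted secondary analyses use age, sex, centre and IQCODE, and do not include delirium status.

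**Objective D.** The aim is: "To determine if DelApp scores are responsive to changes in delirium status and severity for a person over time". The analysis is explicitly limited to data "from patients who have undergone repeat assessments". Score changes, rescaled to a common range across tests, "will be presented in descriptive statistics and graphically, comparing baseline with each of the other time points". The Methods (text under Fig. 1) place 30 patients in this subsample: 15 with delirium at any assessment and 15 without. Each has up to three further assessments, and the reference standard is repeated each time.

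**Group sizes.** Sample size calculation states: "Of the 500 patients recruited, 20% would be expected to have delirium".

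**The concern.** If about 400 of 500 patients have no delirium, a whole-cohort correlation of DelApp with DRS-R98 mixes two things: the gap between delirious and non-delirious patients, and the gradient of severity among the delirious. Only the second speaks to grading severity. The first is already reported as the AUC under the primary objective. It is also partly built in, because DRS-R98 belongs to the reference standard assessment on which the diagnosis rests.

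For objective D, the question is whether a person's DelApp score moves when that person's delirium moves. A baseline-to-visit summary of each test does not make that pairing. Delirium may be present at any of the assessments in the selected patients, so it can emerge after baseline as well as resolve.

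The Discussion presents grading severity and tracking change over time as research uses of DelApp to be evaluated. Statements on both would rest on these two analyses.

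**Working it through.** **The plan's own figures.** No precision is stated for objectives A or D. Table 2 confirms the group sizes: 1.96 × √(0.5 × 0.5/100) = 0.098 for sensitivity and 1.96 × √(0.5 × 0.5/400) = 0.049 for specificity, both as printed. So there are 100 patients with delirium and 400 without.

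**Objective A.** Suppose DelApp and DRS-R98 are unrelated inside the delirium group and inside the non-delirium group. With prevalence π and no ties, the whole-cohort Spearman correlation then has absolute value

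|ρ| = 12 × π(1 − π) × (AUC_DelApp − 0.5) × (AUC_DRS − 0.5).

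At π = 0.20 the leading factor is 12 × 0.16 = 1.92. The documents give no AUC (the pilot's accuracy is called excellent), so the AUCs are assumptions shown as a range. The last column is the share of 2,000 simulated cohorts of 500 with two-sided p < 0.05; the critical |ρ| is 0.088.

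| AUC DelApp / DRS-R98 (assumed) | Calculation | Absolute ρ | Significant |
|---|---|---|---|
| 0.70 / 0.70 | 1.92 × 0.20 × 0.20 | 0.08 | 40% |
| 0.75 / 0.75 | 1.92 × 0.25 × 0.25 | 0.12 | 76% |
| 0.80 / 0.80 | 1.92 × 0.30 × 0.30 | 0.17 | 98% |
| 0.90 / 0.90 | 1.92 × 0.40 × 0.40 | 0.31 | 100% |
| 0.95 / 0.99 | 1.92 × 0.45 × 0.49 | 0.42 | 100% |

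The simulated means agree with the formula. In the same simulations the correlation within the delirium group averaged about 0 and was significant in 4% to 5% of runs, as it should be. With both AUCs at 0.90, |ρ| is 0.21 at 12.5% prevalence and 0.40 at 30%.

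**Objective D, cancellation (illustrative numbers).** Let 8 patients resolve and gain 4 points, 4 become delirious and lose 4, and 18 stay the same. The mean change over all 30 is (8 × 4 − 4 × 4)/30 = 0.53 points. If the 12 who changed are all among the 15 with delirium at some assessment, the mean in that group is 16/15 = 1.07, although the mean absolute change there is 48/15 = 3.2. Splitting the two groups of 15 reduces the cancellation but does not remove it.

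**Objective D, the reverse case.** Simulated changes in 15 delirium patients used t tests on mean change only as a yardstick, since the protocol plans none. With an assumed average recovery of 1 SD on both scales, both mean changes were significant in 91% of runs when individual changes were uncorrelated and in 92% when they correlated at about 0.8. With patients moving in mixed directions and changes correlated at about 0.9, both were significant in 0.3%. A mean change therefore does not distinguish tracking from non-tracking.

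**Precision of the alternatives (Fisher z, 95% CI).** Within delirium, n = 100: 0.11 to 0.47 for ρ = 0.3, and 0.34 to 0.63 for ρ = 0.5. For one change per patient and r = 0.5: 0.17 to 0.73 with n = 30, and −0.02 to 0.81 with n = 15.

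**The case against.** Several points on the other side are sound.

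- **The population for A is not spelled out.** Whole cohort is the plain reading, supported by the explicit restriction given for D in the same section, but the article does not say it. The statistical analysis plan, not shown here, may restrict or stratify.
- **A is a construct-validity aim.** A reader might infer that A fails because it does not show tracking within patients. The document sets no such aim for A; that expectation belongs to D alone.
- **The assumed scenario is stark.** Grouping of participants includes possible delirium and undetermined patients with partial symptoms, so severity is a spectrum and real within-group association is likely. In the two-group model at 20% prevalence the formula cannot exceed 1.92 × 0.5 × 0.5 = 0.48, so a clearly stronger correlation would carry more than the binary split. With weak separation (both AUCs 0.70) the artefact is small.
- **A delirium-only correlation has its own fault.** It leaves out subsyndromal patients and narrows the severity range, which tends to weaken the estimate. That argues for showing both values, and against replacing one by the other.
- **D is exploratory and descriptive.** The plan does not specify a mean over all 30. Results may be shown by group or individual, and the common rescaling allows informal comparison of DelApp with other tests. A descriptive approach suits a purposive sample of 30.

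These points limit the finding but do not remove it. As stated, A's statistic does not separate group difference from severity gradient, and D names no patient-level link although the data for it are collected. The promise of cautious interpretation of secondary analyses does not supply either.

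**Conclusion.** The concern holds in a limited form. On the whole-cohort reading, the delirium/no-delirium difference alone can give objective A an absolute correlation of about 0.08 to 0.42, so a non-zero value does not by itself show that DelApp grades severity. This rests on 20% prevalence (stated), AUCs of 0.70 to 0.95 or above (assumed) and zero within-group association (a worst case, not a prediction). For objective D, the stated summaries do not link a patient's DelApp change to that patient's change in DRS-R98 or status, and pooled summaries can hide opposite changes.

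A reader might go further and infer that neither objective will be answered. The documents do not support that: A's correlation may well contain severity information, and D's graphs may show tracking informally. The accurate statement is that neither is reliably answered by the analysis as described. The primary accuracy analysis is unaffected.

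**What to change.** **Objective A.** State the analysis population. Report the Spearman correlation within the delirium group (about 100 patients) with its 95% CI alongside the whole-cohort value, and base any statement about severity on both.

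**Objective D.** Use the repeated reference standard to report DelApp change by status transition (resolved, new, unchanged). Add a descriptive within-patient association between DelApp and DRS-R98, for example a repeated-measures correlation, with its CI.

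**Cost.** Wording in the analysis plan and a few extra analyses on data already planned. The price is wider intervals: at ρ = 0.5, a full width of about 0.29 for A within delirium (0.63 − 0.34), and about 0.56 for D with 30 patients and one change each (0.73 − 0.17). D should therefore stay descriptive.

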**Methods:**

This is a prospective study of older non-scheduled hospitalised patients (target *n* = 500, age ≥ 65), recruited from elderly care and acute orthopaedic wards. Exclusion criteria are: non-English speakers; severe vision or hearing impairment; photosensitive epilepsy.

A structured reference standard delirium assessment based on DSM-5 criteria will be used, which includes a cognitive test battery administered by a trained assessor (Orientation-Memory-Concentration Test, Abbreviated Mental Test-10, Delirium Rating Severity Scale-Revised-98, digit span, months and days backwards, Vigilance A’ test) and assessment of arousal (Observational Scale of Level of Arousal, Richmond Agitation Sedation Scale). Prior change in cognition will be documented using the Informant Questionnaire on Cognitive Decline in the Elderly. Patients will be categorized as delirium (with/without dementia), possible delirium, dementia, no cognitive impairment, or undetermined.

A separate assessor (blinded to diagnosis and assessments) will administer the DelApp index test within 3 h of the reference standard assessment. The DelApp comprises assessment of arousal (score 0-4) and sustained attention (score 0-6), yielding a total score between 0 and 10 (higher score = better performance). Outcomes (length of stay, mortality and discharge location) will be collected at 12 weeks.

We will evaluate a priori cutpoints derived from a previous case-control study. Measures of the accuracy of DelApp will include sensitivity, specificity, positive and negative predictive values, and area under the ROC curve. We plan repeat assessments on up to 4 occasions in a purposive subsample of 30 patients (15 delirium, 15 no delirium) to examine changes over time.

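### Objective C gives length of stay no post-test starting point and does not adjust for days before the test, so on the ordinary reading part of what DelApp is said to predict has already happened

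*Protocol article*

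**What the plan says.** Four parts of the protocol article bear on this.

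- **Purpose** (Study aims and objectives, objective C): "To assess if DelApp scores predict important clinical outcomes: length of stay, mortality at 12 weeks and discharge destination".
- **Timing of the test** (Study overview): "All patients will be screened in order of arrangement of beds on the respective wards with no limit on duration of patient stay". The only stated constraint is whether a researcher is free. The index test can therefore fall on any hospital day.
- **Analysis** (Statistical analysis plan, Secondary objectives): "the association between DelApp total scores and length of stay, mortality at 12 weeks after study participation and discharge location will be evaluated", using normal linear models. Mortality is timed from entry to the study. Length of stay is given no starting point here, in the objectives or in the abstract, which says only: "Outcomes (length of stay, mortality and discharge location) will be collected at 12 weeks".
- **Adjustment** (same section): the main analyses are unadjusted, and then "We will also present secondary analyses adjusted for age, sex, centre and IQCODE". Days in hospital before the test are not on that list.

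**The concern.** A test result can only predict what comes after it. Unqualified length of stay ordinarily means admission to discharge. On that reading, a patient tested on hospital day 20 has 20 days in the outcome before the predictor exists.

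This does more than add noise if the score itself depends on how long the patient has been in hospital. The article gives a plausible route. It describes delirium as transient and fluctuating (end of Reference standard assessment), and it expects to meet subsyndromal or resolving cases (Grouping of participants). If delirium resolves during the stay, patients reached late tend to score higher and also have long total stays. If delirium arises during the stay, the link can run the other way.

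In either case an association with total stay could be reported as prognostic when it is not, or a real one could be hidden. The planned adjustment would not remove this, because it does not include elapsed days. The issue is the time origin, which is separate from the choice of a normal linear model.

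**Working it through.** **Inputs from the article.** 500 patients (Study overview); two-sided 0.05 tests; unrestricted test day; the covariate list above. The article gives no precision or power figure for objective C. Its Table 2 concerns sensitivity and specificity only. It reproduces (for example 1.96 × √(0.5 × 0.5/100) = 0.098) and is not touched by this point.

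**Assumptions, because the article gives no data.** When in the stay patients are tested, the distribution of stays, and how the score relates to elapsed days.

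**Notation.** e = days from admission to DelApp; r = days from DelApp to discharge; total stay T = e + r.

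**Step 1: share of total stay before the test.** If the test falls at a uniformly random fraction U of the stay, E(U) = 1/2. The share is then 0.50 for any stay distribution (exponential, gamma and log-normal were checked). If testing tends to be earlier, with mean elapsed fractions of 1/3, 1/5 or 1/9, the share is 0.33, 0.20 or 0.11. If everyone is tested on days 0 to 5, with stays averaging about 20 days, it is 0.11 to 0.12. The defensible range is about 0.1 to 0.5.

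**Step 2: can an association appear with no prognostic value?** Let the score have correlation ρ with e and none with r. For exponential stays sampled at a random moment, e and r are uncorrelated with equal SD, so corr(e, T) = 1/√2 = 0.707 and corr(score, T) = 0.707ρ. The chance of a significant result is approximately Φ(z − 1.96) + Φ(−z − 1.96), with z = 0.707 × |ρ| × √500. Simulation used 4,000 studies of 500.

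| Size of ρ | corr with T | z | Approx. | Simulated, total stay | Simulated, remaining stay |
|---|---|---|---|---|---|
| 0 | 0 | 0 | 0.050 | 0.049 | 0.049 |
| 0.05 | 0.035 | 0.79 | 0.124 | 0.127 | 0.045 |
| 0.10 | 0.071 | 1.58 | 0.353 | 0.349 | 0.049 |
| 0.20 | 0.141 | 3.16 | 0.885 | 0.882 | 0.050 |
| 0.30 | 0.212 | 4.74 | 0.997 | 0.997 | 0.052 |

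The sign of the false association is the sign of ρ. At ρ = 0 there is none.

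**Step 3: could ρ differ from zero?** Two assumed courses of delirium bracket the answer, both with random test timing and no effect of the score on remaining stay.

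- *Delirium only resolves.* Exponential stays with mean 14 days, 35% delirious on admission, mean duration 4 to 14 days, score Binomial(10, 0.5) if delirious and Binomial(10, 0.9) if not. Total stay is falsely significant in 78% to 86% of studies, with correlation about +0.12 to +0.13, so better attention appears to go with longer stay. Remaining stay is significant in 4% to 5%.
- *Delirium prevalence constant at 20% throughout the stay.* Total stay is significant in 4.8% to 6.0%, close to nominal, with correlation about zero.

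**Step 4: is a post-test origin enough?** Only if e and r are uncorrelated. Their correlation was 0 for exponential stays, −0.14 for gamma stays of shape 2 (CV about 0.7) and +0.25 for the log-normal stays tried. In the resolving-delirium scenario with CV 0.7, remaining stay was falsely significant in 10% to 17% without adjustment and 6% to 7% with e as a covariate. So e belongs in the model. In a linear model that contains e, the DelApp coefficient is the same for T and for r, because T = e + r and the extra e is absorbed by its own term.

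**The case against.** The strongest reply is that the article never says total stay or stay from admission. It is a condensed account, and the full protocol or analysis plan may define the origin. That stands as a limit: admission to discharge is the ordinary meaning, not a stated one. It does not dispose of the point. The article names the outcome, the model and the covariates, times mortality from study entry in the same sentence, and leaves elapsed days out of the adjustment.

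Second, the share of one half comes from assuming a uniformly random test moment. If wards are revisited and patients are tested soon after arrival, the share is smaller. This stands, hence the range of 0.1 to 0.5.

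Third, a reader might infer that a spurious association is bound to appear, or that it will run in the wrong direction. The documents do not support that. The resolving-only scenario allows no delirium to arise in hospital. With exponential stays it implies only 7.8% to 17.6% delirious at testing, against the article's statement: "Of the 500 patients recruited, 20% would be expected to have delirium". It has no dementia group; adding 25% with intermediate scores (assumed) lowers the false-positive rate to 50% to 72%. Constant prevalence removes the effect. Neither size nor direction is fixed.

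Fourth, stay is one of three outcomes in one of five secondary objectives. The analysis section speaks of association and promises cautious interpretation. This limits the weight of the point, but the stated objective is still to predict.

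**Conclusion.** The point holds in a limited form. The article allows testing on any hospital day, sets out to predict length of stay, gives that outcome no post-test origin and does not adjust for days before the test. On the ordinary reading, some 10% to 50% of the outcome predates the predictor, depending on a timing distribution that the article does not report.

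Whether this biases the result depends on whether scores are related to elapsed days. If they are not, the cost is noise. If they are, even a correlation of size 0.1 would give a false-positive rate of about 35% with 500 patients, and 0.2 about 88%, in either direction. These correlations are assumptions. The course of delirium that the article describes makes a non-zero value plausible but does not establish one.

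The consequence is confined to the length-of-stay part of objective C. The primary accuracy analysis, the cut points and Table 2 are unaffected. The change is worth making because it is cheap and because, without it, a link with length of stay could not safely be read as prediction.

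**What to change.** For the length-of-stay outcome in objective C:

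1. Define it as days from the DelApp assessment to discharge, in line with the origin already used for mortality.
2. Add days from admission to assessment as a covariate in the adjusted stay analysis, and base any statement about prediction on that analysis.
3. Report total length of stay descriptively, together with the distribution of days from admission to assessment, so that readers can see how much of the stay came before the test.

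If the full protocol or analysis plan already defines a post-test origin, only the covariate and the reporting remain.

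The cost is a wording change, one extra covariate and a stay figure less comparable with published total stays. It needs only admission, assessment and discharge dates, which should be available since case notes are consulted. The article describes data cleaning as still under way, so the analysis could still be specified. The working above does not show a need for the covariate in the mortality and discharge-location models, so that extension is not asked for.
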